## 8 **STOPPING RULES**

### 8.1 **Criteria and procedures for premature termination of a subject's research participation**

- Any subject may stop participating in research at any time, for any reason.
- Subject lost to follow-up: the subject's whereabouts are unknown. The investigator must make every effort to reconnect with the subject (and document this in the source file) in order to know at least whether the subject is alive or dead.
- The investigator may temporarily or permanently discontinue a subject's participation in the research for any reason that has an impact on the subject's safety or is in the subject's best interest.
- In the event of premature termination of the subject's participation in the research, his or her data may be used until the date of withdrawal of consent.

In the event of premature termination of a subject's research, or withdrawal of consent, data concerning the subject collected prior to premature termination may be used.

- The observation book should list the various reasons for discontinuing participation in the research:
  - ☐ Undesirable effect
  - ☐ Other medical problems
  - ☐ Subject's personal reasons
  - ☐ Explicit withdrawal of consent.

- Arrangements for replacing these persons, if necessary

No replacement subjects planned.

- Stopping all or part of the search

The AP-HP promoter reserves the right to definitively suspend inclusions at any time, should it prove that inclusion targets are not being met.

## 9 EVALUATION OF EFFECTIVENESS

### 9.1 Description of evaluation parameters of efficacy

The primary endpoint is the change in anterior cingulate cortex activity measured by the change in blood perfusion in ml/100 g tissue/min. The change in blood perfusion of the anterior cingulate cortex after the first exposure (MRI n°2 - MRI n°1) will be compared with the change after the second exposure (MRI n°3 - MRI n°1). MRI n°1 will be performed before the start of the 1st activity session (1st week: 1st exposure), MRI n°2 will be performed after the end of the 2nd activity session, during the last day of activity of the 1st week (1st exposure), MRI n°3 will be performed after the end of the 2nd activity session during the last day of activity of the 3rd week (3rd week: 2nd exposure).

### 9.2 Methods and timetable for measuring, collecting and analyzing evaluation parameters of effectiveness

#### Illustration of a treatment sequence

[figure not shown]

Collection of MRI characteristics (MRI no. 1): blood perfusion of the anterior cingulate cortex (in ml/100 g tissue/min): at the start of the 1st exposure, before the start of the 1st activity session.

Collection of MRI features (MRI no. 2): blood perfusion of the anterior cingulate cortex (in ml/100 g tissue/min): at the end of 1st exposure, after the second activity session.

Collection of MRI features (MRI no. 3): blood perfusion of the anterior cingulate cortex (in ml/100 g tissue/min): at the end of the 2nd exposure, after the end of the last activity session.

## 10 VIGILANCE

In the context of this study, adverse events (serious or otherwise) are not notifiable to the sponsor.

If such events occur, they are related to the pathology or its therapeutic management in the context of care (horticultural and handiwork sessions) and are not related to research. Serious adverse

events will be reported within the framework of the vigilance system set up for the practice under research (radiovigilance ).

The sponsor undertakes to inform the competent authority and the Committee for the Protection of Individuals without delay of the new facts defined in 12° of article R. 1123-46 and, where applicable, of the measures taken.

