| Non-inclusion criteria                             | 
 
- Specific low back pain,
 
- MRI contraindications (metallic equipment, pacemaker, cochlear and intraocular metallic implants, current pregnancy, uncontrollable claustrophobia)
 
- Current work stoppage or work stoppage of more than 3 months in the last year,
 
- No paid employment
 
- Insufficient command of the French language,
 
- Participation in another research project on low back pain
 
- Patients under guardianship or curatorship,
 
- Patients on AME (State Medical Aid)
 
                                                                                                       |
| Acts or products to be researched                  | 2 activities (horticulture and handiwork) are practiced by chronic low-back pain patients. Their effects on activation of the anterior cingulate cortex are compared.                                                                                                                                                                                                                                                                                                                                                                                                                                                                                                                                        |
| Comparator group                                   | The study design is cross-over, with participants being their own controls. The "comparator" intervention is handiwork.                                                                                                                                                                                                                                                                                                                                                                                                                                                                                                                                                                                      |

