| Other acts or procedures added by search           | 
Patients will undergo 3 MRI scans to measure blood perfusion in the anterior cingulate cortex :
 
 
- 1 MRI scan before 1st exposure (beginning of 1st week),
 
- 1 further MRI scan after 1st exposure (end of 1st week)
 
- 1 final MRI at the end of the procedure, after 2nd exposure (end of 3rd week)
 
                                                                                                                                                                                                                                                             |
| Expected benefits for participants and the company | 
If successful, this study will enhance the therapeutic arsenal available to treat chronic low-back pain patients. Horticultural therapy could be a precision non-pharmacological intervention for people with chronic low back pain, targeting both the neurobiological and physical aspects of exercise deconditioning.
                                                                                                                                                                                                                                                                                                                                                                              |
| Minimal risks and constraints added by research    | 
The risks are minimal:
 
 
- related to the adverse events most frequently reported during moderate-intensity physical activity: pain, fatigue and musculoskeletal injuries.
 
- related to handling handiwork and gardening (injuries)
 
- related to MRI: presence of metal equipment, pregnancy, uncontrollable claustrophobia
 
- related to the patients' walk between Cochin and Sainte-Anne hospitals (patients will be accompanied by a member of the rehabilitation team during these journeys).
 
 
Patients have to travel to the Cochin hospital (4 times in 3 weeks), take part in craft and horticultural therapy
 |

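### Section 10 declares every adverse event unrelated to the research, which contradicts the synopsis and fails even on the protocol's own split between care and research

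*Protocol*

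**What the plan says.** Section 10 (Vigilance) makes three statements.

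- Notification: "adverse events (serious or otherwise) are not notifiable to the sponsor".
- Causality: for any that arise, the text holds that "they are related to the pathology or its therapeutic management in the context of care (horticultural and handiwork sessions) and are not related to research".
- Route for serious events: they go through the "vigilance system set up for the practice under research (radiovigilance"). The sponsor also undertakes to pass new facts to the competent authority and the ethics committee without delay.

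The synopsis takes a different line. Its row headed "Minimal risks and constraints added by research" includes risks "related to the adverse events most frequently reported during moderate-intensity physical activity: pain, fatigue and musculoskeletal injuries", risks "related to handling handiwork and gardening (injuries"), MRI risks and the walk between the two hospitals. The same row counts attending the sessions as a constraint on patients. The row on what is being researched says that "2 activities (horticulture and handiwork) are practiced by chronic low-back pain patients" and that their effects are compared.

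Section 2.6 repeats the activity harms and the walk of about 1 km as risks for research subjects. Section 2.4 describes both activities as established routine care in the department. Section 2.5 names brain MRI as the procedure that the research adds.

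**The concern.** The same harms are presented as brought by the research in one place and as having nothing to do with it in another. Section 10 also settles relatedness by rule, before any event has happened. Relatedness is normally a judgement made on each event by the investigator.

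This is a pilot of lifting, carrying, bending and tool use in people with chronic low back pain, and one of the two activities is called the experimental intervention. If the rule is followed as written, a fall on the way to the scanner or an incident in the MRI unit is classified as unrelated to the research. A participant who has a pain flare or a minor injury and still completes the study has no stated place where that event is recorded. The sponsor's promise to report new facts then rests on information that the protocol gives it no stated way to receive.

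**Working it through.** The point is a conflict of text, so the check sets the sections side by side. The plan has no figure to reproduce.

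**1. Are the activity harms research risks?** Synopsis risk row: yes, and session attendance is a research constraint. Section 2.6: listed among the risks for research subjects. Section 2.4: the activities are routine care. Section 10: events in the sessions belong to care and are unrelated to research. Section 6.3, the table meant to separate care from research, enters NA under care in both rows and puts the sessions in neither column. The protocol gives no single answer.

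**2. Does Section 10 hold if the sessions are accepted as care?** Take Sections 2.4 and 2.5 at face value.

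- MRI: Section 2.5 and Section 6.3 both place it with the research. Section 10 covers all adverse events without excepting it.
- Walk: Section 5.2 puts the scanner at another hospital 1 km away, with patients accompanied there on foot. The synopsis says they walk to the other hospital for this examination. The walk therefore follows from the research MRI.

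On the protocol's own split, the rule is wrong for these two sources of events.

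**3. Does the stated route cover the events?** Section 10 describes the route as the one for the practice under research and calls it radiovigilance. The synopsis says the practices under research are horticulture and handiwork. The only imaging is MRI, without contrast (Section 2.5), and the recruitment brochure in the appendices tells patients that it does not irradiate. Nothing shows that the route covers a tool injury, a back injury, a fall on the walk, or an MRI incident.

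**4. Does the protocol name any record of events?** The data described in Section 4.1, Sections 6.1.2 to 6.1.4 and Section 6.2 contain no adverse-event item. Section 8.1 lists undesirable effect among the reasons for stopping participation, which captures only events that end participation.

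**5. Extent of exposure.** With 2 sessions in each of 2 exposure periods, a participant has 2 × 2 = 4 sessions. For 16 participants this is 4 × 16 = 64 participant-sessions. With 3 MRI scans each, there are 3 × 16 = 48 scans, each reached on foot. These are maxima that assume no loss to follow-up; the protocol allows for 20%.

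**The case against.** The best defence is that Section 10 follows from a coherent framing. Both activities are ordinary care in this department (Section 2.4), the research adds only MRI (Section 2.5), the study is classed as minimal risk (Section 15), and the imaging act has its own vigilance route. On that reading the outlier is the synopsis row. This stands in part: the documents do not settle whether the sessions are care or research, so a reader should not assume that the synopsis is right about them. It does not save the blanket sentence, which fails for MRI and the walk on that same framing.

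A reader might infer more than the text supports.

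- *That a serious event would reach neither the sponsor nor the analysis.* Section 10 does name a route and commits the sponsor to report new facts. Section 15.8 allows the information note and consent form to be revised if adverse effects occur. What is missing is a stated path that fits these events.
- *That the e-CRF has no adverse-event page.* The form is not shown. Only the protocol's own data lists can be read.
- *That not notifying the sponsor breaches the rules.* That depends on regulations outside the documents and is not judged here.
- *That Section 13 should tabulate harms.* That may sit in a statistical analysis plan.
- *That patients are randomised to one activity or the other.* Only the order is randomised; all are planned to receive both.

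Symptoms are not wholly unobserved: Section 4.1 repeats the Roland-Morris and SF-12 questionnaires at baseline and after each exposure. They measure limitation and quality of life, however, and do not count events. Several SF-12 items also look back 4 weeks, longer than the 3 weeks of participation.

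**Conclusion.** The contradiction is real and should be corrected. Section 10 assigns causality in advance for every adverse event, against the synopsis for the activity harms, MRI and the walk, and against Sections 2.5 and 6.3 for MRI and, by consequence, the walk. Its named route does not evidently cover these events, and the protocol's data lists name no adverse-event record apart from one discontinuation reason.

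The size is best given as scope: three sources of events (sessions, walk, MRI) across up to 64 participant-sessions and 48 scans. A bound on event rates from 16 patients would not measure this fault. The primary endpoint and its test are untouched.

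The conclusion rests on reading Section 10 as covering all adverse events, since it states no exception, and on the walk being made only for the scan, as Section 5.2 and the synopsis describe it. It does not depend on whether the sessions are finally classed as care or as research.

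**What to change.** - Remove from Section 10 the sentence that declares all adverse events unrelated to the research.
- Reconcile the synopsis risk row with Sections 2.4, 2.5, 2.6, 6.3 and 10, stating for the sessions, the walk and the MRI whether each is care or research, and enter the sessions in the Section 6.3 table.
- State a vigilance route that covers each of the three and gives the sponsor the information it needs to honour its new-facts commitment. Clarify the term radiovigilance against the brochure's description of MRI.
- Record adverse events in the e-CRF by exposure period and activity, with the investigator's judgement of relatedness for each event.

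The cost is one additional e-CRF form, an amendment to Section 10 with matching edits in the sections above, and a small amount of data entry for 16 patients over 3 weeks.

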## **11 SPECIFIC RESEARCH COMMITTEES**

### **11.1 Steering Committee**

The steering committee will be composed of :

The coordinating investigator [name], the scientific manager, Doctor [name], the methodologists in charge of the project: Doctor [name], the managers of the URC/ CIC Paris Descartes Necker/Cochin or the Project referent of the URC/CIC Paris Descartes Necker/Cochin.

The role of the steering committee is to :

- Define the general organization and progress of the research, and coordinate information.
- Determine the methodology at the outset, and decide during the course of the research what to do in the event of unforeseen circumstances.
- Monitor the search process.

## **12 DATA MANAGEMENT**

### **12.1 Data collection methods**

Clinical and paraclinical signs will be collected and entered into an electronic data collection notebook (e-CRF CleanWEB), with access restricted by a login and password, unique to each investigating physician in charge of a patient. The data entered will be anonymized and secured by encryption during data transfer. The sponsor will use the information concerning the participant in accordance with the objectives of the study or for any additional scientific research.

### **12.2 Right of access to source data and documents**

- Data access

In accordance with GCP :

- the sponsor is responsible for obtaining the agreement of all parties involved in the research to guarantee direct access to all research sites, source data, source documents and reports for quality control and audit purposes by the sponsor,
- investigators will make available to the persons responsible for monitoring and quality control, in the event of an audit of research involving the human person, the documents and individual data strictly necessary for this control, in accordance with the legislative and regulatory provisions in force

- Source documents

Source documents, defined as any original document or object that can be used to prove the existence or accuracy of data or facts recorded during the course of the research, will be kept for 15 years by the investigator, or by the hospital in the case of hospital medical records.

All data comes from the medical record, except for questionnaires, which are collected directly from patients and entered into e-CRF.

- **Data confidentiality**

Those responsible for quality control in research involving the human body (article L.1121-3 of the French Public Health Code), will take all necessary precautions to ensure the confidentiality of information relating to the research, to the persons involved, and in particular to their identity, and to the results obtained.

These people, like the investigators themselves, are bound by professional secrecy (under the conditions defined by articles 226-13 and 226-14 of the French penal code).

During or at the end of research involving the human person, data collected on subjects and transmitted to the sponsor by the investigators (or any other specialist) will be rendered non-identifying.

Under no circumstances may the names or addresses of the persons concerned appear in clear text.

Only the initials of the surname and first name will be recorded, together with a coded number specific to the research indicating the order of inclusion of subjects.

Similarly, if the results of this study are published, the participant's identity will remain confidential.

These data may also be transmitted to the French health authorities or to other entities of the promoter, under conditions that ensure their confidentiality.

The sponsor will ensure that each person taking part in the research has given his or her written consent for access to individual data concerning him or her and strictly necessary for the quality control of the research.

### **12.3 Data processing and storage of documents and data**

- **Identification of the data controller and data processing location**

All data will be entered into an electronic CleanWeb data collection notebook (e-CRF). The Unité de Recherche Clinique Paris Centre will be responsible for research data management and database management (Manager: Pr [name], Deputy Manager: [name] [name]).

- **Data entry**

Non-identifying data will be entered electronically via a web browser.

### **12.4 Data ownership**

The AP-HP is the owner of the data and no use or transmission to a third party may be made without its prior agreement.

## **13 STATISTICAL ASPECTS**

Intention-to-treat study

Quantitative variables will be described by their means and standard deviation, and qualitative variables by their absolute and relative frequencies.

Depending on the normality of the distribution of the quantitative variables of interest, they will be compared using a rank comparison test (Wilcoxon test) or a mean comparison test (Student's t-test for paired samples).

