| Number of subjects selected                       | Sample size is estimated at 16 participants. We predict a mean difference in variation in anterior cingulate cortex blood perfusion of 7 ml/100 g tissue/min with a standard deviation of 4, a power of 90%, an $\alpha$ risk of 5% and a potential lost to follow-up of around 20%.                                                                                                                                                                                                                                                                                                                                                                                                                                                                                                                                                                                                                                                                                                                                                                                                                                                                                                                                                                                                                                                                                                                                                                                                                                                                                                                                                                                                                                                                                                                                                                                                                                                                                                                                                                                                                                                                                                                                                                                                                                   |

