### 7.3 Recruitment procedures

*Justification of recruitment capacity with regard to the number of subjects to be included ;*

A difference of 7 ml/100 g tissue/min (SD=4) between perfusion changes in the anterior cingulate cortex after the 2 horticultural therapy sessions and after the 2 handiwork sessions is estimated to be clinically relevant (Bratman et al., 2015). Given this expected difference, a risk  $\alpha$  of 5%, a power of 90%, and a potential lost to follow-up of 20%, we planned to include a total of 16 patients.

Participants will be recruited from among patients seen in consultation by a doctor in the department or a doctor attached to the department. Participants will also be informed of the study by means of posters displayed in the Department of Re-education and Rehabilitation of the Musculoskeletal System and Spine Pathologies at Cochin Hospital, and in the waiting rooms of the private practices of doctors attached to the department (Appendix J and K). A patient included in the study will be able to call on his or her own network of acquaintances (recruitment based on the snowball effect). In the department it is during a consultation that the physician (-investigator) asks the patient if he or she agrees to be contacted by telephone about a study.

|                                                   | Number of subjects |
|---------------------------------------------------|---------------------------|
| Total number of subjects selected          | 16                        |
| Number of recruiting centers               | 1                         |
| Inclusion period (months)                  | 12                        |
| Number of subjects / center                | 16                        |
| Number of subjects / center / month | 1,3                |

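### The named paired t-test or Wilcoxon test leaves period out of a randomised two-sequence cross-over; a period-adjusted test would keep the estimate unbiased and the confidence interval correct at little cost

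*Protocol*

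**What the plan says.** Section 13 opens with "Intention-to-treat study". It then gives descriptive statistics and one rule for comparisons. Its outcome is that "they will be compared using a rank comparison test (Wilcoxon test) or a mean comparison test (Student's t-test for paired samples". Which of the two applies is left to a distributional check, worded as "Depending on the normality of the distribution of the quantitative variables of interest". The statistical row of the synopsis (Section 1) repeats the rule. No period or sequence term appears in either place.

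The design is a cross-over with 1:1 randomisation to two sequences (Section 5.1). Section 4.1 sets MRI #2 minus MRI #1 against MRI #3 minus MRI #1. Section 5.3.2 explains that three weeks was chosen to limit the influence of natural symptom evolution on the primary endpoint, and judges a one-week wash-out sufficient. Section 7.3 plans for "A difference of 7 ml/100 g tissue/min (SD=4) between perfusion changes in the anterior cingulate cortex after the 2 horticultural therapy sessions", set against the change following handiwork. The remaining planning figures there are "a power of 90%, and a potential lost to follow-up of 20%, we planned to include a total of 16 patients". On withdrawals, Section 8.1 says: "No replacement subjects planned".

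**The concern.** MRI #1 is common to both changes and cancels, so the primary comparison is MRI #2 against MRI #3 within each patient, about two weeks apart. Anything that moves perfusion between those scans for every patient, such as getting used to the scanner or the natural course of symptoms, is a period effect. Section 5.3.2 treats change over time as a threat to the primary endpoint, yet the named tests cannot separate it from treatment.

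A paired test pools both sequences into one sample. A period effect then does two things. It adds spread to the differences, because it raises them in one sequence and lowers them in the other. If the sequences differ in size, the two contributions no longer cancel in the mean. A pilot exists largely to supply an estimate and an interval, and those are what would be distorted.

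**Working it through.** **Inputs.** Difference 7 and SD 4 (Sections 1 and 7.3), with SD 4 read as the SD of the within-patient treatment difference. Alpha 5%, taken as two-sided because sidedness is not stated. 16 patients, 1:1, about 20% loss, so about 13 complete. The period shift is not given; 2 to 4 ml/100 g/min is assumed. A true difference of 4 is used beside 7 to show behaviour below the design effect; it is also an assumption.

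**The plan's own figure.** A paired t-test with difference 7 and SD 4 needs 6 pairs for 90% power, and 6/0.8 = 7.5, so 8 after loss. A two-independent-groups formula gives 7 per group, 14 in all, then 14 × 1.2 = 16.8 (17) or 14/0.8 = 17.5 (18). The stated 16 is near the second figure, not the first. Nothing below depends on how 16 was reached.

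**Structure.** Let τ be horticulture minus handiwork and π the period shift (MRI #3 minus MRI #2 with no treatment difference).

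- Sequence A (horticulture first): mean difference = τ − π.
- Sequence B (handiwork first): mean difference = τ + π.
- Paired mean: τ + π(nB − nA)/n, so its bias is π(nB − nA)/n.
- Period-adjusted estimate, (mean A + mean B)/2: τ whatever the split, with SE = (σ/2)√(1/nA + 1/nB) on n − 2 df.

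**Equal sequences, 8/8.** Bias is zero. The expected variance used by the paired test is σ² + π² × n/(n − 1):

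- π = 3: 16 + 9 × 16/15 = 25.6, SD about 5.06.
- π = 4: 16 + 16 × 16/15 = 33.1, SD about 5.75.

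The true SE is 4/√16 = 1.00, but the paired test works with about 5.06/4 = 1.26 or 5.75/4 = 1.44. Its interval is therefore roughly 26% or 44% wider than it should be.

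**Unequal sequences.**

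- 8/5: size of bias = 3 × 3/13 = 0.69 and 4 × 3/13 = 0.92 ml.
- 9/4: 4 × 5/13 = 1.54 ml.

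If 8/8 are randomised and 3 of 16 are lost at random, an 8/5 split (either way round) has probability 2 × C(8,3)/C(16,3) = 112/560 = 20%. A 9/4 split cannot arise from 8/8; it needs sequences already unequal at randomisation.

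**Simulation, paired t-test against period-adjusted t-test, SD 4**

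| Split | Shift | Type I error, paired | Power at τ = 4, paired / adjusted |
|---|---|---|---|
| 8/8 | 0 | 5.0% | 96% / 96% |
| 8/8 | 2 | 2.9% | 93% / 96% |
| 8/8 | 3 | 1.5% | 89% / 96% |
| 8/8 | 4 | 0.6% | 81% / 96% |
| 8/5, bias against the effect | 3 | about 3.5% | about 60% / 89% |
| 8/5, bias against the effect | 4 | about 2.6% | about 40% / 89% |
| 9/4 | 2 | 6.9% | not used |
| 9/4 | 4 | about 8% | not used |

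The adjusted test holds about 5% throughout. When the imbalance runs with the effect, the paired test can have more power than the adjusted one (at 8/5 and shift 2, 93% against 89%), but only because its estimate is biased in that direction.

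**At the design effect of 7.** Paired power is at least 99.9% at 8/8 and at least 98% at 8/5 in either direction, for shifts up to 4.

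**Price of adjusting when there is no shift, τ = 4.** At 7/6: 91.1% against 90.5%. At 8/5: 91.0% against 89.0%. At 9/4: 91.3% against 86.1%.

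**Normality check.** Choosing between t and Wilcoxon after a normality test left type I error between 4.9% and 5.3% for normal, t(3) and Laplace differences at n = 13 and 16.

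**The case against.** The shift is hypothetical. Nothing in the protocol suggests 3 to 4 ml, which is about half the target effect, and the short schedule and wash-out are meant to keep such change small. With no shift the paired test is valid and slightly more efficient. In most scenarios the error is on the conservative side, and at the planned effect the power is ample. All of this stands. It limits the size of the concern but does not remove it, because the protection costs one degree of freedom and is needed exactly when the hope of no shift fails.

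Three stronger readings are tempting, and the document does not support them.

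- **That the study wastes power.** At 7 with SD 4 it does not; the loss needs a smaller effect, or a larger SD, together with a sizeable shift.
- **That the plan analyses complete pairs only and so breaks its intention-to-treat label.** The protocol nowhere writes this. Section 8.1 allows data collected before withdrawal to be used, and the definition of the analysis set and the handling of missing scans commonly sit in the SAP. Using first-period-only patients would shrink the SE by only about 1 to 5%.
- **That the normality check spoils the error rate.** The figures above show it does not. Nor does the text establish that raw values are checked: the primary endpoint is itself a change. What remains is that the primary test is not fixed before the data are seen.

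**Conclusion.** The point holds as a conditional one. The protocol fixes, in two places, a test that ignores period in a randomised two-sequence cross-over. If a period shift of 3 to 4 ml/100 g/min exists, equal sequences give an unbiased estimate with an interval that is too wide and a conservative test (type I error 1.5 to 0.6%). An 8/5 split adds a bias of 0.7 to 0.9 ml, and type I error passes 5% only at strong imbalance (about 8% at 9/4). The shift is an assumption, SD 4 is taken as the SD of the paired difference, and the power figures were obtained for the t-test, not the Wilcoxon test. The benefit of changing is an unbiased estimate and a correct interval, not more power at the planned effect. It is a cheap improvement to a pilot rather than a fault that invalidates it.

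**What to change.** In the statistical row of Section 1 and in Section 13, replace the normality-driven rule with one pre-specified primary analysis of horticulture versus handiwork adjusted for period. Either of these would do:

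- the two-sequence cross-over t-test, i.e. the mean of the two sequence means with pooled variance on n − 2 df; or
- an equivalent linear model with patient, period and treatment and a small-sample df correction.

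State the contrast by treatment, report it with a 95% CI, and use the same analysis for the rumination and dramatization scores. As a sensitivity analysis, use the rank test that compares within-patient period differences between the two sequences.

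The cost is protocol wording and one degree of freedom. With no period effect and a true difference of 4, that is under 1 point of power at 7/6, about 2 points at 8/5 and about 5 points at 9/4.
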